### Randomization, allocation concealment, and blinding

After eligibility and consent are confirmed and a baseline survey is completed, participating clinicians will be randomized at a ratio of 1:1 to one of the two study arms. An electronic randomization list will be generated using the latest version of the statistical software platform R (version 3.3.2, http://www.r-project.org). The list will be securely integrated into the cloud-based Research Electronic Data Capture (REDCap) tool. Allocation will be concealed from all investigators and staff until the study group is assigned. Only the study manager and research assistants involved in the delivery of the intervention components will subsequently be made aware of allocation. It is not possible to mask participating clinicians; however, their patients will have no knowledge of their potential participation in weekly teleECHO sessions, monthly interactive webinars, and quarterly short courses. All staff who are involved in the collection of data and investigators who conduct analyses will remain blinded to allocation throughout the study.

### Retention and withdrawal

In order to enhance retention in the study, all participating clinicians will be offered CME credit at no cost for their engagement in weekly teleECHO sessions and monthly interactive webinars. Clinicians will also be offered the flexibility to temporarily pause participation in sessions as an alternative to fully withdrawing. Participation in this study is voluntary. Participating clinicians may decide not to participate or may leave the study at any time. This decision will not result in any penalty or loss of benefits to which they are entitled. Information that has already been collected may still be used, but no new information will be collected. The withdrawal reason and the withdrawal date will be documented.

Clinicians who go on a leave of absence (LOA), while participating, will not be contacted about the study. Patients assigned to participating clinicians on LOA will remain a part of that clinician’s LC&FIRP patient assignment. However, if the patient seeks follow-up care, they will be scheduled to see another clinician participant in the same intervention arm. Additionally, clinicians who terminate their employment with FHCSD, retire, or move departments and are unable to see primary care patients will be withdrawn from the study. All of the data that they contributed up to the point of withdrawal will be included in the research. Patients assigned to clinicians who withdraw from the study will be reassigned to another participating clinician in the same intervention arm. Clinician participants who choose to temporarily pause participation will not be assigned new patients but will continue to see existing LC&FIRP patients within their panel.

### Intervention(s)

Of the 20 participating clinicians, 10 will be randomized to weekly teleECHO sessions. It is both impractical and inconsistent with high ethical standards to prevent the remaining 10 clinicians from accessing the dissemination of best practices via monthly interactive webinars and quarterly short courses, as these will be made available to providers across the USA. The subsections below provide more details on the intervention and an overview of the flow of clinicians through the study can be found in Fig. 1.

**Fig. 1 Fig1:**
[figure not shown]
Flow of clinicians through the study

#### Weekly teleECHO sessions

The weekly teleECHO sessions will include a 10- to 20-min subject matter expert (SME)-led didactic presentation of emerging evidence-based best practices, followed by interactive review and discussion of 1–2 cases presented by clinicians for consultation with the multidisciplinary specialty panel. All weekly teleECHO sessions will offer CME credit for participants. De-identified case forms will be submitted by clinicians, and these will include patient medical and family history, current diagnoses, medications, and the clinician’s proposed inquiry to panelists. The composition of the specialty panel will include, but will not be limited to, national experts in pulmonology, neurology, neuropsychology, psychiatry, infectious disease, cardiology, rehabilitation medicine, and lived experience experts. Additional specialists will rotate and participate on a regular basis, and cases will be scheduled for presentation in an attempt to align with guest panelists. Upon conclusion of weekly teleECHO sessions, multidisciplinary recommendations will be distributed back to the presenting clinicians.

#### Monthly interactive webinars

We will convene monthly interactive webinars to rapidly disseminate findings and emerging best practices to a large-scale, national audience. The series will offer brief didactic presentations by SMEs, examples of models of care, and a facilitated question and answer session. The target audience will include clinicians participating in LC&FIRP, as well as primary care clinicians across the USA. The program will expand attendance by offering CME, Continuing Nursing Education (CNE), and Continuing Pharmacy Education (CPE) credit and engaging with organizations and associations outside the LC&FIRP partners through various dissemination strategies. These strategies include invitation to the monthly interactive webinar through existing listservs that reach these organizations’ and associations’ current members, as well as collaborative efforts in cross promotion on the LC&FIRP specific Project ECHO web page. Project ECHO will send an announcement for each webinar via email using a mass mailing platform and include the following information: title of Project ECHO program, session date and time, registration link, agenda, topic, speaker presentation slides (if available), and CME accreditation statements. In addition, Project ECHO will maintain the LC&FIRP specific Project ECHO web page and post agendas, video recordings, and resources shared during the monthly interactive webinars.

#### Quarterly short courses

Key findings from weekly teleECHO sessions will be consolidated into singular topics and delivered in quarterly short courses. These quarterly short courses will be formatted using multiple learning modules with the use of presentation slides and videos online that are accessible asynchronously. Following each module, there will be a set of questions learners will answer to review the material. There will be a post-course quiz at the end of each course with a score of 70% resulting in the printing of a certificate of completion. Each course will take less than an hour to complete. The target audience will include clinicians participating in LC&FIRP and primary care providers across the USA. Similar to the monthly interactive webinar, these quarterly short courses will be disseminated through existing partner channels, as well as organizations and associations collaborating with all project partners. To partake in the quarterly short course, learners must register through the University of Colorado’s (UoC) web page. Once published online, the quarterly short course will remain available until the next quarterly short course is published.

## Measures

### Clinicians

#### Quarterly survey

Data will be collected from all clinicians participating in the LC&FIRP, both intervention and control groups. Data collection is designed to document reported changes to provider knowledge, self-efficacy, and clinical behavior as a result of participating in the intervention or control conditions. The objectives of documenting these changes are to (1) help explain effects of the intervention on patient outcomes, including by comparing providers in the control arm based on reported changes to knowledge, self-efficacy, and behavior and (2) answer the co-primary implementation research question of this effectiveness-implementation trial: was the intervention implemented effectively and was it acceptable and feasible to implement among providers outside of the study context?

Data will be collected using electronic, web-based surveys, administered through REDCap managed by FHCSD. Surveys will be administered quarterly, to align with the collection of patient outcome data during the first 12 months. This frequency will also facilitate providers’ recall of specific changes to practice or behavior or improvements in knowledge in the last reporting period. Afterward, clinician survey data will be collected at the 18-, 24-, and 30-month mark. We anticipate the survey to take 8–12 min for each provider and comprise approximately 30 questions. The survey will remain open for a select period and reminder emails will be sent to encourage compliance.

Survey constructs and question formats are drawn from a deep body of existing research evaluating the impact of ECHO models on clinicians’ outputs and outcomes [15]. Survey methods and constructs were also studied among all randomized controlled trials of clinician-level outcomes globally captured in the Health Care Provider Performance Review, a multi-year systematic literature review process of global health worker performance evaluations [24]. To measure knowledge and self-efficacy, providers will be asked to state their relative agreement with statements related to their care of PCC patients, measuring from “strongly agree” to “strongly disagree” [15]. This 5-point response format will be held constant across survey knowledge and self-efficacy statements, to allow for an index to be created for use in more exploratory analyses. Open-ended response fields will be provided to some questions to allow providers to document specific examples of practice changes. Lastly, constructs probing overall provider satisfaction and utility with content will be measured to inform the acceptability and feasibility of the intervention.

#### Weekly teleECHO sessions

During the last 10 min of each weekly teleECHO session, intervention clinicians will be asked to follow a link to a web-based survey, loaded in REDCap. This semi-structured survey has three objectives: (1) to gather data required for the participants to receive CME credit, (2) to gather data useful for assessing feasibility and utility of the teleECHO model, and (3) to gather data on format and content of the sessions to guide program improvement. CME credit is offered by Project ECHO, University of New Mexico (UNM) to intervention providers who attend each session. To be eligible for this credit, clinicians are required to complete 20 post-session questions that are universal for every teleECHO session, which explore session relevance, achievement of course objectives, pace and delivery of the session content, and what participants liked most or least about the session. Additionally, we ask clinicians to rate their knowledge of the session content before and after the session, to explore knowledge gains, and if and how they intend to apply course content to their care of patients with PCC, ME/CFS, and other PIFI patients.

Making time within the session for this survey and making these questions mandatory for CME credit is expected to result in better survey compliance. The survey will last approximately 10 min and we will leave the survey available for a short time after the session to help clinicians complete the survey who might have been interrupted for any reason. If survey compliance is under 50%, a reminder email will be sent in a timely manner prior to the survey closing. Intervention clinicians’ survey responses will not be strictly confidential, as the questions are required to be documented by individuals for CME credit. With every survey, we will encourage clinicians to be candid in their responses, so that we can improve the ability of the teleECHO session curriculum to meet their needs. While this lack of anonymity presents a risk for bias, we will have the opportunity to assess similar constructs of utility and satisfaction in the quarterly surveys of participating clinicians, which will be strictly confidential and de-identified. This will help us to assess any bias and take further measures to reduce bias if needed.

#### Monthly interactive webinar

Data collected regarding the monthly interactive webinar will include webinar attendance and post webinar surveys for all clinicians participating in the Randomized Control Trial. Project ECHO UNM will offer CME, CNE, and CPE credits to all LC&FIRP participants and external learners for each monthly interactive webinar. This post-webinar survey will include a standard set of 23 questions that the Project ECHO UNM team requires for attendees to receive educational credits. The objective of collecting monthly interactive webinar data is to (1) understand the relative participation by study clinicians in monthly interactive webinars as a means to interpret differences in primary clinicians’ outcomes and (2) to support the evaluation of the feasibility, acceptability, and sustainability of the intervention. Survey responses will not be strictly confidential, as the questions are required to be documented by individuals for CME, CNE, or CPE credit. The survey will remain available after the monthly interactive webinar for 3 business days. If a participant misses that window and wants to claim credit, the ECHO survey team can reopen the survey if it is within 30 days of the webinar. After clinicians complete the survey, they will receive a certificate via email.

#### Quarterly short course

Data will be collected passively on numbers of clinicians completing each quarterly short course modules. The active collection of data will include responses by the clinicians to knowledge-based questions after each module, and at the completion of each course, about the value of the sessions and courses. The post-quarterly short course survey will include 10 questions about the knowledge gained, attitude changes that resulted from participation, and potential plans for behavioral changes resulting from what participants have learned. Measures collected from the post-quarterly short course survey for LC&FIRP participants and other learners will mirror the monthly interactive webinar survey. The objective of collecting quarterly short course data is to (1) understand the relative participation by study clinicians in monthly interactive webinars as a means to interpret differences in primary clinicians’ outcomes and (2) to support the evaluation of the feasibility, acceptability, and sustainability of the intervention. In addition to collecting data immediately before and following participation in the quarterly short course, LC&FIRP participants in the study will be asked to provide their responses to surveys that are specific to the trial outcomes.

#### Patients

Upon assignment to a participating clinician participant, patients will be asked to share current demographic characteristics, symptoms, medical history, health history, and, if applicable, their initial acute COVID-19 experience. Patients will be asked to complete a variety of widely used and validated patient reported outcome surveys that will take an average of 30 min to complete and will be repeatedly collected at 3-, 6-, 9-, and 12-months. In addition, symptom history and, if applicable, initial acute COVID-19 experience questions will be repeated during quarterly surveys to measure any changes over the 12-month follow-up period. Given the diverse nature of symptomatology, the patient cohort will first be characterized using descriptive statistics on domains of dysfunction (e.g., neurologic, cardiac, pulmonary, mental health). Surveys will include (1) Patient-Reported Outcomes Measurement Information System (PROMIS)-29, (2) Health Assessment Questionnaire (HAQ), (3) PROMIS Dyspnea Functional Limitations Short Forms, (4) PROMIS Applied Cognition Abilities and General Concerns Short Forms, (5) Patient Health Questionnaire (PHQ-9), (6)Generalized Anxiety Disorder (GAD)-7, (7) self-reported medication use, and (8) CDC ME/CFS Symptom Inventory Grid Screener [25–28]. All patient data collected will be integrated into the clinical workflows to maximize the likelihood of consistent completion. To track and collect patient surveys, a registry will be created within CMIS which includes specific survey forms for each survey frequency. All surveys completed will be stored within EHR and accessible for participating clinicians to review. Surveys will be conducted via phone calls from FHCSD staff supporting LC&FIRP, with calls ranging from 30 to 90 min.

Each patient will be called a maximum of four times over the course of 4 weeks (once per week) to ensure the best possibility of achieving responses. Upon request, patients may request a copy of their survey responses. Patients who are unreachable for their 12-month survey or are unable to do the survey over the phone will be offered a shortened online version that includes the PROMIS-29 survey to be sent via text or email. An overview of the patient flow throughout the study can be seen in Fig. 2.

**Fig. 2 Fig2:**
[figure not shown]
Patient flow through the study. *LC&FIRP PCP follow-up appointments may occur more than once

#### Physical therapy assessment

Upon completion of their initial assessment, patients will be asked to complete a physical therapy (PT) LC&FIRP visit. During their PT visit, patients will be asked to complete a variety of widely used and validated physical therapy assessments. These assessments include a 2-min step test, 30-s sit to stand test, grip strength, functional gait assessment, and balance tasks [29–33]. Due to appointment time constraints, not all assessments will be completed and additionally patients may decline or be unable to complete some assessments. All patient data collected during the PT visit will be stored in a specific form within the EHR and accessible to participating clinicians for review. Alternatively, patients may choose to decline participation in a PT visit, and this will not impact their ability to meet with their assigned clinician participant. Patients who completed an initial PT visit will be offered to schedule a final PT PCC visit during their 12-month follow-up survey call with FHCSD staff.

#### Wearables

A 20% (*n* = 172) subsample of the patients assigned to clinician participants will be offered a Fitbit device for remote monitoring. Patients will be offered a Fitbit randomly when agreeing to complete their PT visit or by clinician participants and PT providers who believe they may benefit from receiving one to help manage their symptoms. Patients will be asked to verify they have access to a smart phone and if they agree, they will be asked to wear their device as often as possible throughout the 12-month follow-up period. The Fitbit device will collect data on multiple physical activity metrics (e.g., intensity, steps, bouts of exercise), sleep metrics (e.g., time in/out of bed, sleep stages, sleep quality), physiology of the heart (e.g., beats per minute, heart rate variability), and, depending on circumstances, cardiorespiratory fitness. These data will be used to obtain a better understanding for the phenotype(s) of PCC, ME/CFS, and other PIFI. Data collected from Fitbit devices will automatically be uploaded to Fitabase, a Fitbit API partner who will provide a platform for FHCSD to view clean data ready for analysis. At the end of the patient’s 12-month review, their data will no longer be shared with Fitabase and they will be allowed to keep their device.

### Researchers

Researcher generated data will be collected by FHCSD staff supporting LC&FIRP through EHR chart review and survey data including clinical changes to practice, participation in interventions available, exposure to interventions, and patient experience. For all clinicians participating in the Randomized Control Trial, the changes to practice will be measured by the volume of total patient case load, volume of PCC and ME/CFS patient case load, and number of referrals made to specialists at the established intervals of 3-, 6-, 9-, 12-, 18-, and 30-months post baseline. For the 10 intervention clinician participants, assessment of changes to practice will include proportion of cases presented to a multidisciplinary specialist panel and number of specialist recommendations applied from case consultation. In addition, for the 10 intervention clinicians, we will measure the participation and exposure to topics in weekly teleECHO sessions, as well as participation in presenting case forms. For all 20 clinician participants, we will review participation in monthly interactive webinars and quarterly short courses and exposure to topics discussed in each, respectively. We will conduct an EHR chart review to measure the number of specialists seen by a patient and specialty types they were exposed to during their 12-month follow-up period. The objective of this data collection is to inform patient and clinician outcomes and support assessment of the feasibility, acceptability, and sustainability of the intervention.

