### Study design

We will evaluate LC&FIRP using an effectiveness implementation hybrid type 2 design [16]. Specifically, we will conduct a two-arm, single-blind, pragmatic, quality improvement, professional cluster, randomized controlled trial in which 20 consenting clinicians across primary care clinics at FHCSD will be randomized at a ratio of 1:1 to either participate in (1) weekly teleECHO sessions with monthly interactive webinars and quarterly short courses or (2) monthly interactive webinars and quarterly short courses alone (a control group). All clinicians will have the option to receive Continuing Medical Education (CME) credit for the weekly teleECHO sessions and monthly interactive webinar. More details on the content of the weekly teleECHO sessions, monthly interactive webinars, and quarterly short courses are provided below. Clinicians will participate in LC&FIRP up to 37 months and throughout participation, 856 FHCSD patients diagnosed with PCC, ME/CFS, or other PIFI will be assigned to the participating clinicians (approximately 42 patients per clinician). Patient outcomes will be evaluated according to the study arm of their respective clinicians. Quantitative and qualitative outcomes will be measured at 3-, 6-, 9-,12-, 18-, 24-, and 30-months post-baseline for clinicians and for patients at 3-, 6-, 9-, and 12-months post assignment to a participating clinician. We will concurrently conduct a prospective cohort study to compare the two patient populations resulting from the randomized controlled trial with a third patient population resulting from enrollment at University of Washington’s Post-COVID Rehabilitation and Recovery Clinic (https://www.uwmedicine.org/specialties/post-covid-rehabilitation). An overview of the study period for clinicians and patients can be found in Table 1.

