## Discussion

This study will provide much needed high-quality evidence on the effectiveness of a technology-enabled multi-disciplinary team-based care model for the management of PCC, ME/CFS, and other PIFI within an FQHC setting, while simultaneously providing evidence regarding the feasibility, acceptability, and sustainability of the approach. Given that LC&FIRP includes a teleECHO program that is case-based, interactive, and occurs in real-time, it has a set of distinct advantages to the traditional practice of sequential in-person specialty referrals to address complex patient cases. This may be particularly helpful for cases in which the etiopathogenesis of PCC, ME/CFS, and other PIFI is unclear, as multiple specialist perspectives may be generated and discussed with the treating primary care clinician. It may also improve the targeted referral to local specialists to minimize unnecessary overuse of specialty care and reduce patient travel and time burden. We expect that the knowledge and confidence of participating clinicians will increase over time, that the cases presented to specialists will become more complex, and simpler routine cases will require consultation less frequently. This approach, which is clinician-focused, is nonetheless likely to result in more rapid provision of high-quality care for patients. We acknowledge that common clinical issues related to PCC, ME/CFS, or other PIFI will likely change over time. We consider our ability to measure this variation and explore its effect on a variety of clinician and patient outcomes as a strength. Taken together, findings from this research should inform how primary care providers and health system leaders support the clinical care of patients suffering from PCC, ME/CFS, and other PIFI.

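### PCC and ME/CFS caseload and an undivided referral count are weak measures of changed clinician practice, because both move with the patient panel the trial assigns

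*Protocol article*

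**What the plan says.** The Researchers subsection under Measures defines practice change for every randomized clinician: "the changes to practice will be measured by the volume of total patient case load, volume of PCC and ME/CFS patient case load". A third item, counted for the same clinicians, is the "number of referrals made to specialists at the established intervals of 3-, 6-, 9-, 12-, 18-, and 30-months post baseline". All three items are volumes, and no denominator is given. For intervention clinicians only, it adds "proportion of cases presented to a multidisciplinary specialist panel and number of specialist recommendations applied from case consultation". A separate chart review will "measure the number of specialists seen by a patient and specialty types they were exposed to during their 12-month follow-up period". As to purpose, the subsection says of these data: "The objective of this data collection is to inform patient and clinician outcomes and support assessment of the feasibility, acceptability, and sustainability".

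Other sections determine how patients reach a clinician. Under Study design, the 856 enrolled patients "will be assigned to the participating clinicians (approximately 42 patients per clinician"). Recruitment, enrollment, and study duration lets both participating and non-participating clinicians refer patients into the programme. Under Retention and withdrawal, a clinician who pauses receives no new patients, and "Patients assigned to clinicians who withdraw from the study will be reassigned to another participating clinician in the same intervention arm".

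Statistical analysis compares change from baseline in clinician-level outcomes between arms with a linear mixed model. It also models change over time in the intervention clinicians alone, using GEE with log-binomial or Poisson models.

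**The concern.** A measure of changed practice should move when clinicians manage patients differently and stay still when they do not. Two of the three volumes do not meet that test.

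The PCC and ME/CFS caseload rises because the study sends patients, and shifts when colleagues pause or withdraw. It also omits other PIFI, although such patients are enrolled and assigned on the same footing.

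The referral count depends on how many patients a clinician has as well as on how often that clinician refers. While the panel fills, the count can rise although referral behaviour is unchanged or has moved the other way. At stake is the reading of the practice-change results, which are meant to help explain patient outcomes and to support the implementation conclusions.

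**Working it through.** **Inputs from the protocol article.** 856 patients, 20 clinicians, 10 per arm (Study design; Participants). The pause and reassignment rules are in Retention and withdrawal. That section also says no new information is collected after a clinician leaves, so a withdrawn clinician is missing afterwards and is not counted as zero.

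**Planned panel.** 856 / 20 = 42.8 patients per clinician, which agrees with the stated figure of about 42. Per arm: 856 / 2 = 428. With equal assignment, the assigned part of the caseload has an expected arm difference of 42.8 − 42.8 = 0, whatever the intervention does. That part cannot show an effect. A difference in it would come from uneven assignment, pauses or withdrawals.

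**Referral count over time.** Write count = panel × referrals per patient. The ratio of two counts is then the panel ratio times the rate ratio, and the starting rate cancels. The protocol gives no referral rate and no schedule of panel growth, so the starting panels below are assumptions, each growing to 42.8:

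| Starting panel | Panel ratio | Count ratio, rate unchanged | Count ratio, rate halved |
|---|---|---|---|
| 10.7 | 4.00 | 4.00 | 2.00 |
| 21.4 | 2.00 | 2.00 | 1.00 |
| 32.1 | 1.33 | 1.33 | 0.67 |

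At an assumed 1 referral per patient, the first row is 10.7 referrals rising to 42.8. With the rate halved it is 10.7 rising to 0.5 × 42.8 = 21.4. The count doubles while the behaviour halves. The table takes the count over assigned patients. If it covers a clinician's whole practice, which the text leaves open, the effect is diluted by the other patients.

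**Between arms, equal panels.** The difference in mean counts is 42.8 × (intervention rate − control rate). It is zero if and only if the rates are equal, so the comparison still reflects behaviour.

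**Between arms, unequal withdrawal.** Assume the arm's 428 patients have all been assigned and clinicians then withdraw from that arm only. However the patients are shared out, the mean over those remaining is:

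- 1 of 10 withdrawn: 428 / 9 = 47.6, and 47.6 / 42.8 = 1.11 (+11%).
- 2 of 10 withdrawn: 428 / 8 = 53.5, and 53.5 / 42.8 = 1.25 (+25%).

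At an identical referral rate, mean referrals per clinician from assigned patients rise by the same percentages against an arm with no withdrawals.

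**The case against.** The best defence has five parts.

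1. **Assignment does not set everything.** Total caseload includes a clinician's other patients, and the decision to refer to a specialist is the clinician's own. Participating clinicians can also refer patients into the programme, so even the PCC and ME/CFS caseload partly reflects recognition and diagnosis. This stands: the point covers that caseload and the undivided referral count, and says the first is largely, not wholly, driven by the trial.
2. **The randomized comparison cancels a common rise.** Planned assignment is equal and reassignment stays within the arm. This stands in expectation. It does not help the intervention-only GEE analysis, which has no control group to remove panel growth.
3. **Behaviour is measured elsewhere.** The Quarterly survey covers reported clinical behaviour in both arms, with room for specific examples, and the chart review records specialists seen per patient. This stands in part. The proportion of cases presented and the recommendations applied exist in one arm only, the survey is self-report by unmasked clinicians, and specialists seen per patient is not named as practice change.
4. **A denominator or offset is analysis-plan detail.** Caseload and referrals are both collected, so a rate could be formed later. This would answer a silence. Here the text fixes the measures as volumes, and no offset turns assigned caseload into behaviour.
5. **No direction is claimed.** The remark that the approach may "improve the targeted referral to local specialists to minimize unnecessary overuse of specialty care" is a hedged sentence in the Discussion, and the tests are two-sided. This stands, and is a reason to read the referral rate descriptively.

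A reader might infer that study caseload runs from 0 to about 43 and that both arms will therefore show a large false change. The documents do not establish a baseline of 0: participating clinicians are described as already caring for such patients, and existing diagnoses are admitted. A reader might also expect leave of absence to move panels. It does not, because those patients stay in the absent clinician's assignment. Only the clinician seen for follow-up changes.

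**Conclusion.** The point holds in a limited form and is worth correcting. PCC and ME/CFS caseload is a weak marker of changed practice. The undivided referral count confounds panel size with behaviour when followed over time, and most clearly in the intervention arm alone.

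The over-time distortion can be large: a fourfold rise at an unchanged rate if the panel grows from 10.7 to 42.8, which is an assumed path. The between-arm distortion is about zero with equal panels. It reaches 11% with one withdrawal, or 25% with two, confined to one arm after full assignment. Those withdrawals are also assumptions.

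The stronger reading, that the practice-change measures record logistics and no behaviour at all, is not supported. Total caseload and the referral decision are not set by the trial, and other measures of behaviour are planned. These are supportive outcomes; the primary outcome, the sample size and the randomized patient comparison are untouched.

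**What to change.** In the Researchers subsection:

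- Report caseload for PCC, ME/CFS and other PIFI as workload and as a denominator, and remove it from the practice-change measures.
- Analyse specialist referrals per assigned LC&FIRP patient per interval, or as a Poisson count with assigned patients as the offset. The listed time points are unequally spaced (3 months apart up to month 12, then 6 and 12 months), so patient-months would be the safer exposure if counts accrue between them.
- Attribute each referral to the clinician responsible at the time, where the EHR allows. This matters because leave and withdrawal both change who sees a patient.
- State in advance that a change in the referral rate, in either direction, is descriptive and not in itself a benefit.

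The cost is small. Caseload and referrals are already to be collected at the same time points. One listed practice-change measure becomes a descriptor, and the planned chart review must link referrals to assigned patients. The text does not show that this link is already made, so the change may need some extraction work as well as wording.
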